### Recruitment

For an estimated study period of 2 years, all patients randomised to an intervention or control ICU bedspace as part of the RCT or admitted to environmental control bedspaces as part of the case–control study will be screened for suitability to participate in the research study. Suitable patients will be approached by a member of the research team as soon as possible after admission to ICU, in consultation with the treating clinical team. As patient status commonly changes throughout ICU admission, patients may be screened daily until discharge and may be recruited to the study at any time during their admission to ICU if suitable based on the following inclusion/exclusion criteria:

#### Inclusion criteria

Patient residing in AustraliaPatients sufficiently fluent in English to complete recruitment and data collection processesPatients expected to remain in ICU for > 24 h

#### Exclusion criteria

Patient or legal representative unable or unwilling to provide consent.Patients less than 18 years of age.Death is deemed imminent.Patient deeply or moderately sedated (RASS score ≤  − 3).Recent substantial neurological insult (e.g. stroke).Patient deemed agitated, aggressive, or displays unpredictable behaviour.

Patients will be informed of the purpose and aims of the study and informed consent will be obtained prior to being enrolled in the study. If patients are unable to consent, the substitute decision-maker or next-of-kin will be approached to consider participation. Figure 2 summarises the enrolment, intervention, and assessment timeline.

**Fig. 2 Fig2:**
[figure not shown]
Study schedule of enrolment, intervention, and assessments

Patients for whom consent is obtained will complete the study components listed below. Based on annual admission numbers and current admission diagnoses and presentations, the average number of patients eligible for randomisation per bedspace in the study facility is approximately 30 per year. We therefore estimate that approximately 250 patients will be randomised over 2 years. We expect that approximately 50 patients will be ineligible for participation for various reasons and based on other studies in the unit we have conservatively estimated a 50% patient decline rate. We therefore estimate that approximately 100 patients will provide consent and be recruited to this study over the 2-year study period.

A power calculation for this study is not possible, due to the lack of studies reporting the impact of environmental upgrades on patient outcomes. Therefore, an interim analysis will be conducted after 6 months of data collection, focussing on recruitment rate, completion rate for the various study components, and in-hospital outcome measures, with a power calculation performed based on this data to determine the number of participants required.

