The impact on patients may extend beyond admission, with disrupted sleep and delirium contributing towards the development of post-intensive care syndrome (PICS), a collection of complications including cognitive, physical, mental, and psychological disability, which affects up to 80% of patients discharged from critical care [24, 25]. The ongoing health problems and disability associated with PICS can severely impact the quality of life of patients and their families [26, 27]. Many ICU survivors never return to work and require significant caregiver support. This may detrimentally impact on their family members’ ability to work and their earning capacity, leaving them unable to provide for the family financially, with close to one third of patients reporting losing most or all family savings and their major source of income after serious illness [28]. Associated personal, social, and economic costs are immense.

To redress these issues, investment should be targeted towards solving these widely recognised design problems and evaluating the outcomes of environmental upgrades. Previous studies have suggested that a modified ICU environment is associated with a reduced delirium rate and ICU length of stay [29]. However, to date, there are limited studies directly investigating the relationship between ICU bedspace environmental upgrades and patient outcomes [30].

The ICU of the Future project is a mixed-method project, aiming to improve the ICU bedspace environment and assess impact on patient outcomes. This project commenced with modifiable environmental, technological, and design features contributing to suboptimal outcomes being identified via qualitative patient, family, and staff interviews [4, 31] and quantitative studies [32]. This was followed by a co-design process, used to redesign and develop an innovative and adaptive ICU bedspace capable of being individualised to patients’ personal and changing needs and aimed to optimise clinical efficiency, patient experience, and outcomes [33]. The new bedspace design has been implemented in the study ICU with patients admitted from January 2023. Table 1 summarises the main changes to the implemented bedspaces.

**Table 1 Tab1:** Main changes implemented for the upgraded bedspaces

Environmental factor addressed	What was implemented
Sound/noise reduction	
1. Improved sound absorption	1. Acoustically absorbent ceiling tiles and walls (satisfying infection control criteria) and softer floor vinyl

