#### RCT component

The primary study assessing patient outcomes (study components 3–6 described below) is an RCT, in which the two upgraded bedspaces are defined as intervention, while the 25 ‘conventional’ bedspaces serve as control. Eligibility screening, consent, and randomised allocation is a two-step process. All patients admitted to ICU are eligible to be randomised 1:1, except those deemed unsuitable for admission to the intervention bedspaces:

Patients requiring extracorporeal membrane oxygenation, intra-aortic balloon pump, or dialysisPatients admitted to ICU immediately following cardiac surgery, including transplantation

Patients will be randomly assigned to bedspaces as follows:

A random sequence of allocations to intervention and control bedspaces was established by the research coordinator and sealed in numbered, opaque envelopes. ICU floor coordinators and clinical personnel are blinded to this sequence until revealed at randomisation.Randomisation is completed by the ICU floor coordinator/admitting ICU doctor when:At least one intervention and one control bedspace are available at the time a patient is accepted for admission.The patient is eligible for randomisation (see above).The ICU floor coordinator or responsible clinician on duty opens the next envelope in sequence to reveal allocation of the patient to an intervention or control bedspace.The patient is assigned to the allocated bed.Patients will then be assessed for eligibility for participation in the study by a member of the research team (see ‘Recruitment’ section below).

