### Data collection and monitoring, study components, and data analysis

Data describing participant demographics and ICU admission will be collected from hospital records and recorded on case report forms (CRFs). Data collected will include date of birth, gender, hospital and ICU length of stay, ICU and hospital survival, ICU readmission rates, mechanical ventilation time, details of their illness, medical treatment, and existing comorbidities. Completed CRFs will be entered into an electronic database. Patient characteristics and ICU admission data will be described using summary statistics. The number of patients approached and consented will be charted, together with the number who dropped out or died.

A data monitoring committee was not considered as this was a low-risk intervention. Data monitoring and study conduct is reviewed 6 monthly by the research investigators and submitted for ethics committee review yearly.

In addition to data from the study components being individually analysed and reported as described below, data analysis will also investigate the relationships between different outcomes/components. Inter-related components that will be explored include whether observed differences in sleep architecture is correlated with changes in delirium outcomes, and whether a difference in the maintenance of circadian rhythm between intervention and control bedspaces impacts the incidence of PICS at 6-month post-ICU discharge.

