To our knowledge, this is the first study to investigate the impact of large environmental upgrades on patient outcomes in the ICU setting. The strengths of this protocol include the rigorous and multi-dimensional evaluation of both patient outcomes and experiences. The group of consumers (former ICU patients and their families) that helped co-design the upgraded ICU bedspaces also provided feedback and essential input into how they felt the bedspaces should be evaluated and therefore the study design, ensuring we are evaluating what is important to ICU patients. Limitations include that the study is conducted at a single site with a specific local context, potentially impacting on generalisability of data. Also, as only two bedspaces have been upgraded, the small number of beds will limit the number of patients we are able to recruit to the study. A prolonged data collection period, with regular interim data analyses, has been chosen for this reason to ensure sufficient data is collected to be able to compare the intervention bedspaces with control bedspaces. Additionally, there were no perfectly matched beds for the case–control sub-study. When the doors are closed, the implementation bedspaces function like a single room; however, the doors are much wider than the other single rooms in the unit making them functionally closer to open-plan bedspaces when the doors are open. Considering all the other single rooms have windows, it was therefore decided that the bedspaces closest in function and design to the implementation bedspaces were the three chosen open-plan and windowless ones. Lastly, during the upgrade of the two bedspaces, there were multiple changes made to the design, function, and technology in the bedspaces. Should the upgraded bedspaces demonstrate improved patient outcomes, it will not be possible to determine which feature(s) of the intervention bedspaces that contribute to these improvements, or their proportion towards contribution.

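### The number of participants is to be set from outcome data on about 25 people, with neither outcome nor parameter named; if the observed difference is used, that number is close to noise

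*Protocol article*

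**What the plan says.** All references are to the protocol article.

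- **Recruitment, text after Figure 2.** The forecast is that "approximately 250 patients will be randomised over 2 years", and that after ineligibility and refusals "approximately 100 patients will provide consent and be recruited to this study over the 2-year study period". A power calculation is called impossible because too few studies report what environmental upgrades do to patient outcomes. As a consequence, an interim analysis after 6 months will look at recruitment, completion of the components, and "in-hospital outcome measures, with a power calculation performed based on this data to determine the number of participants required".
- **RCT component.** "The primary study assessing patient outcomes (study components 3–6 described below) is an RCT". These components cover sleep, circadian rhythm, delirium and outcomes at 6 months. The article singles out none of them as the outcome on which the trial is sized.
- **Discussion, limitations.** Because two beds restrict recruitment, "A prolonged data collection period, with regular interim data analyses, has been chosen for this reason", so that there will be enough data to compare intervention with control bedspaces.
- **Data collection and monitoring.** There is no data monitoring committee. "Data monitoring and study conduct is reviewed 6 monthly by the research investigators".

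**The concern.** The sizing rule is something the article states, not something it leaves out, and three features of it are weak.

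1. It works on outcome data from the first quarter of accrual, which is very few people.
2. It does not say which outcome is used. Restricting it to in-hospital measures removes the 6-month questionnaires but still leaves sleep, circadian, delirium and length-of-stay measures, each of which would give a different number.
3. It does not say which parameter is taken from the data. The input described as missing is the impact of the upgrade, and the interim is introduced as the remedy, so the natural reading is that the observed between-arm effect goes into the formula.

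A number set this way could end the trial far too small, or show a requirement that two beds could not meet in the planned period. Resizing on the observed effect, or testing the arms at the further looks mentioned in the Discussion, would also raise the false-positive rate unless the final analysis allows for it.

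**Working it through.** **Inputs from the article.** About 30 patients eligible for randomisation per bedspace per year; two intervention beds; 1:1 allocation; 2 years; about 250 randomised; about 50 ineligible; 50% decline; interim at 6 months.

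**Assumptions (not in the article).** Uniform accrual, an equal split, two-sided 5%, 80% power, and the effect sizes shown. Non-randomised case–control patients are not counted.

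**1. The plan's own figures.**
- Randomised: 2 beds × 30 × 2 years × 2 arms = 240, consistent with approximately 250.
- Consented: (250 − 50) × 0.50 = 100. Reproduced.
- Consented at 6 months: 100 × 6/24 = 25, or 12 to 13 per arm.

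**2. If the observed effect is used.** Total N = 2 × ⌈2 × ((1.960 + 0.842)/d)²⌉, with d the difference in SD units. At d = 0.5 this gives 2 × 63 = 126. The standard error of d on 12.5 per arm is √(2/12.5 + 0.5²/50) = 0.406, so an observed 0.5 carries a 95% interval of −0.30 to 1.30. Simulating 13 against 12 patients 400,000 times and putting the observed d into the formula gives:

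| True difference | Correct total N | Interquartile range of calculated N | Under half the correct N | Over twice the correct N | Wrong sign |
|---|---|---|---|---|---|
| 0.3 SD | 350 | 88 to 1090 | 42% | 31% | 23% |
| 0.5 SD | 126 | 52 to 440 | 31% | 34% | 10% |
| 0.8 SD | 50 | 26 to 112 | 22% | 27% | 2% |

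At 0.5 SD the middle 80% of calculated totals runs from 28 to 2568. Wrong-sign trials are sized on the absolute difference, so they overlap the other columns.

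**3. If only the SD or an event rate is used.** An SD on 23 degrees of freedom has 95% limits of 0.777 to 1.403 times the estimate. N scales with its square, so the required N lies between 0.60 and 1.97 times the calculated one. With the difference fixed at 0.5 SD and 12 per arm, the simulated total N has median 122 and a 95% range of 64 to 210. For a binary outcome seen in 8 of 25 (illustrative), the exact 95% interval is 15% to 54%.

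**4. Type I error, nominal 5%.**

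| Use of the interim data | Type I error |
|---|---|
| N stays at 100, no early claim | 5.0% |
| N reset from the SD only | about 5.2% |
| N reset from the observed effect, unadjusted final test (minimum N 25 to 100, maximum 200 to 400) | 5.6% to 7.7% |
| Unadjusted tests at 25 and 100, either of which can claim success | 9.1% |
| Unadjusted tests at 25, 50, 75 and 100, each able to stop the trial | 12.6% |

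**5. What 100 participants can detect.** (1.960 + 0.842) × √(2/50) = 0.56 SD at 80% power. Power for 0.5 SD is about 70%.

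**The case against.** The strongest reply is that the article says only that the calculation rests on the interim data. That is compatible with taking an SD or event rate from them and combining it with a chosen difference, which is a respectable design. This stands: use of the observed effect is an inference from the reason given, and under the milder reading the number is imprecise, not noise. The case–control sub-study collects the same measures in similar beds, so an SD or rate need not rest on 25 people alone. But the article does not say that this is the plan, and its own explanation points the other way.

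A reader might also infer several stronger points that the documents do not support:

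- **That the 5% level is broken.** The article gives no significance level, no efficacy test at a look and no stopping rule. Boundaries may sit in the full protocol or the analysis plan. The inflated figures above are conditional, and the number of looks is an illustration.
- **That one interim and regular interims contradict each other.** Announcing one analysis does not exclude others. What is missing is their content.
- **That investigators will see outcomes by arm.** The six-monthly review is described as covering data monitoring and study conduct, and it is not linked to the interim analyses.
- **That 100 is a ceiling.** It is a forecast using a decline rate described as conservative, over a period described as estimated. Fewer refusals or a longer period would raise it.
- **That the Background contradicts the Recruitment section.** The Background reports that "a modified ICU environment is associated with a reduced delirium rate and ICU length of stay", but goes on to say that direct studies of bedspace upgrades are limited. That agrees with a lack of studies as the reason for having no power calculation.

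**Conclusion.** The concern holds in a limited form. The sizing rule as written takes in-hospital outcome data at one quarter of forecast accrual, about 25 participants, and fixes neither the outcome nor the parameter. Used with the observed effect, as its rationale suggests, it would return a total below half or above twice the correct one in about 65% of trials at a true 0.5 SD (31% + 34%). Used with an SD only, it would be right to within a factor of about two. The error rate is unprotected rather than shown to be lost: the plausible excess ranges from almost none to 12.6%, depending on choices that the article leaves open. A later analysis plan could settle adjustment for the looks, but it cannot make 25 patients informative about an effect.

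**What to change.** **In Recruitment:**
- Name the single outcome on which the trial is sized.
- State that the 6-month recalculation uses only arm-blind quantities: the SD over both arms combined or the overall event rate, with consent and completion rates. Data from the case–control beds may support the SD or rate.
- Combine these with a smallest worthwhile difference fixed before any outcome data are examined.
- State what about 100 participants can detect: about 0.56 SD at 80% power and two-sided 5%.

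An SD taken without regard to arm includes part of any true difference. At 0.5 SD it raises the variance, and so N, by a factor of 1 + 0.5²/4 = 1.06, which is a small price.

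**In the Discussion:** say that interim reviews cover recruitment, completeness and these arm-blind quantities only. If a between-arm look is wanted, say that it is prespecified and that the final analysis is adjusted for it.

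**Cost:** wording only, provided it is done before interim outcomes by arm are seen. The investigators give up early between-arm results, and the stated detectable effect will look large.

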### Data collection and monitoring, study components, and data analysis

Data describing participant demographics and ICU admission will be collected from hospital records and recorded on case report forms (CRFs). Data collected will include date of birth, gender, hospital and ICU length of stay, ICU and hospital survival, ICU readmission rates, mechanical ventilation time, details of their illness, medical treatment, and existing comorbidities. Completed CRFs will be entered into an electronic database. Patient characteristics and ICU admission data will be described using summary statistics. The number of patients approached and consented will be charted, together with the number who dropped out or died.

A data monitoring committee was not considered as this was a low-risk intervention. Data monitoring and study conduct is reviewed 6 monthly by the research investigators and submitted for ethics committee review yearly.

In addition to data from the study components being individually analysed and reported as described below, data analysis will also investigate the relationships between different outcomes/components. Inter-related components that will be explored include whether observed differences in sleep architecture is correlated with changes in delirium outcomes, and whether a difference in the maintenance of circadian rhythm between intervention and control bedspaces impacts the incidence of PICS at 6-month post-ICU discharge.

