#### Component 5: delirium prevalence

The prevalence of delirium will be assessed by the completion of the confusion assessment method for the intensive care unit (CAM-ICU) twice per day (morning and afternoon) for all enrolled patients by a member of the research team.

Delirium data analysis will involve:

The prevalence and incidence of delirium will be calculated and compared between intervention and control bedspaces.Comparison of cases and non-cases on demographic and diagnostic data and length of stay will be undertaken using methods appropriate to type of data: T-tests, chi square, and ANOVA.

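### The 6-month look at in-hospital outcomes should be limited to pooled data, because the research team recruits after the bed is known and scores delirium

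*Protocol article*

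**What the plan says.** **Interim analysis.** The sample size paragraphs at the end of the Recruitment section say that no power calculation is possible, "due to the lack of studies reporting the impact of environmental upgrades on patient outcomes". They therefore plan an interim analysis after 6 months, "focussing on recruitment rate, completion rate for the various study components, and in-hospital outcome measures". Its results feed a calculation that sets how many participants are needed.

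**Further looks.** The Discussion, under limitations, says: "A prolonged data collection period, with regular interim data analyses, has been chosen for this reason". It gives neither interval nor content.

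**Oversight.** The section on data collection and monitoring declines a data monitoring committee because the intervention is low risk. It continues: "Data monitoring and study conduct is reviewed 6 monthly by the research investigators and submitted for ethics committee review yearly".

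**Recruitment and rating.** Under RCT component, a research team member assesses eligibility for the study after the bed has been assigned. Under Recruitment, the rule reads: "Suitable patients will be approached by a member of the research team as soon as possible after admission to ICU". The treating team is consulted. Patients may be rescreened daily and enrolled at any point in the ICU stay. Under Component 5, CAM-ICU is completed twice a day "for all enrolled patients by a member of the research team".

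**Masking.** The only masking described is concealment of the allocation sequence until randomisation.

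**The concern.** An interim look at outcomes in an open trial does least harm when those who can still influence the data do not see the arms compared. Here two routes of influence stay open after the look.

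- **Enrolment.** Patients enter the study after the bed is known. Some exclusions are matters of judgement, such as being considered agitated or unpredictable, and that criterion plausibly overlaps with delirium, which is itself an outcome.
- **Delirium rating.** CAM-ICU is a bedside assessment made by the research team. The upgraded bedspaces have added doors, a virtual window and an artificial skylight, so a rater at the bedside can be expected to know the arm.

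A team that has seen an early difference could, without intending to, enrol or rate in line with it. The low-risk argument for having no committee concerns safety. It does not bear on whether interim comparisons are kept confidential.

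**Working it through.** **1. The plan's recruitment figure.** Inputs from the Recruitment section: about 250 randomised, about 50 ineligible, 50% declining.

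(250 − 50) × (1 − 0.50) = 100. The stated figure of about 100 participants is reproduced.

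Upstream, 30 eligible per bedspace per year × 2 upgraded beds × 2 years × 2 arms (1:1) = 240, which is consistent with approximately 250.

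**2. How much of the trial follows the first look.** The article gives no accrual curve, so uniform accrual over 24 months is assumed. Enrolled at month m = 100 × m/24.

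| Month | Enrolled | Still to enrol |
|---|---|---|
| 6 | 25 | 75 |
| 12 | 50 | 50 |
| 18 | 75 | 25 |

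Only month 6 is a stated time for an outcome analysis. Months 12 and 18 show how the exposed share would shrink if any of the regular analyses fell there. If the power calculation raised the target above 100, the share still to enrol at month 6 would exceed 75%.

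**3. What a comparison by arm could show at month 6.** With 25 participants there are about 12.5 per arm. The article gives no delirium rate, so 20% to 40% is assumed. The 95% half-width for a difference is 1.96 × √(2p(1−p)/12.5):

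- p = 0.20: 31 percentage points
- p = 0.30: 36 percentage points
- p = 0.40: 38 percentage points

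The half-width for the pooled rate is 1.96 × √(p(1−p)/25):

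- p = 0.20: 1.96 × √(0.16/25) = 16 percentage points
- p = 0.30: 1.96 × √(0.21/25) = 18 percentage points
- p = 0.40: 1.96 × √(0.24/25) = 19 percentage points

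A difference by arm at this point would be mostly noise, yet it could look large to those who see it. The pooled rate, which a power calculation can use, is estimated with half the half-width.

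**4. Does the plan imply a look by arm?** The gap it names is the effect of the upgrade. Pooled data give a variance or an event rate but not that effect. The Discussion also ties its interim analyses to being able to compare intervention and control bedspaces. A look by arm is therefore the natural reading, but it is not stated, and a pooled look is not excluded.

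**5. Do the sections agree on the looks?** Recruitment describes one outcome analysis, at 6 months. The Discussion describes several, at no stated interval. The monitoring section describes a 6-monthly review of data monitoring and study conduct and does not mention outcomes. The article does not say how the three relate.

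**The case against.** Several stronger readings are tempting, and the article does not support them.

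- A reader might infer that in-hospital outcomes go to the investigators every 6 months, giving three exposures before enrolment ends. The 6-monthly review is of data monitoring and study conduct. The only dated outcome analysis is the one at 6 months.
- A reader might infer that nobody outside the project would see a harm signal. The review goes to the ethics committee each year, and a reason is given for having no committee. Nothing here shows that reason to be wrong for changes to acoustics, lighting and entertainment.
- A reader might take it as fact that the recruiting and rating staff will learn the trend. The text says neither that results are shown by arm nor that the investigators who read them are the people who recruit or score CAM-ICU. Overlap is plausible at a single site, but it is an inference.

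It can also be said that recruitment after allocation and rating by the research team carry a risk of bias without any interim look. That is true, and pooling the look does not remove it. The rule is to approach patients promptly and with the treating team, which limits discretion. Survival and length of stay come from hospital records, and sleep recordings are read by sleep scientists, so these outcomes are less exposed than CAM-ICU.

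Finally, who holds interim results is a detail that an article may leave to the full protocol. This carries weight, but the article does more than stay silent: it fixes an outcome look, gives a reason that points to the arms, and names the investigators as reviewers. What remains is an avoidable added risk.

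**Conclusion.** The point holds as a design weakness that is cheap to remove. The article commits to an outcome analysis at 6 months and to further analyses at no stated interval, and it does not restrict them to pooled data. Staff from the research team still control enrolment after allocation and score delirium.

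Under uniform accrual, about 75 of 100 participants would be enrolled and rated after the first look. That figure measures how much of the trial is exposed; it is not an estimate of bias, which the article gives no means to size. The conclusion rests on two inferences: that the look would be by arm, and that its result would reach those who recruit or rate. Both are plausible, and neither is stated. A pooled-only rule makes both harmless, and the sample size can still be set.

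**What to change.** 1. **Recruitment section, sample size paragraphs.** State that interim in-hospital outcomes are reviewed pooled across arms only. State that the power calculation uses the pooled variance or event rate together with a target difference fixed before the look.
2. **Same place.** State that any tabulation by arm is kept from everyone who screens, seeks consent or scores CAM-ICU until enrolment and rating have ended.
3. **Recruitment, data monitoring section and Discussion.** Give one consistent number and timing of interim looks. Say whether the 6-monthly investigator review includes outcome data and, if so, that these are pooled.

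The cost is a few sentences. No committee or extra safety role is needed for this purpose. The small downside is that investigators do not see the comparison between arms until the end. The team must also choose a target difference on its own judgement, rather than take one from about 12 to 13 participants per arm.
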